## Limitations

One of the main limitations of the study is that the intervention will only be carried out in one session, so if doubts arise among the participants after the face-to-face session, they cannot be resolved by the physical therapist, and this could harm the interpretation and acquisition of information. In addition, since PNE is little known by the general population, the expectation of the effectiveness of the therapy can significantly influence the results. Finally, the physical therapist who will apply the PNE will not be blinded. However, both experimental groups will be instructed to deliver the content in the same way.

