**Methods:**

A three-arm randomized controlled trial will be conducted. Sixty-nine participants with CLBP will be recruited in a 1:1:1 ratio. Participants, assessor, and statistician will be blinded to group assignment. The PNE intervention will be adapted to the context of the participants. An experimental group (*n* = 33) will receive PNE in an in-group modality, the other experimental group (*n* = 33) will receive PNE in an individually modality and the control group (*n* = 33) will continue with usual care. Additionally, participants will be encouraged to stay active by walking for 20–30 min 3–5 times per week and will be taught an exercise to improve transversus abdominis activation (bracing or abdominal following). The outcome measures will be fear avoidance and beliefs, pressure pain threshold, pain self-efficacy, catastrophizing, pain intensity, and treatment expectation. Outcome measures will be collected at one-week before intervention, immediately post-intervention, and four-weeks post-intervention.

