### Intervention

The content of the intervention will be identical in the experimental groups. The only difference is that the PNE in the in-group modality (G1) is provided in groups of 3–5 participants, while in the individual modality (G2) it is provided directly to a single participant. The intervention has an active educational approach based on reconceptualizing the maladaptive beliefs that influence the fear-avoidance behavior of the participants through updated contents of the neuroscience of pain. This will be delivered in a single face-to-face session of approximately 60–80 min in the kinesic clinic of the Santo Tomás University and will be delivered through active participation encouraging synchronous discussion of the information and allowing note-taking. A break will be made in the middle of the session to allow the participants a break. Five key domains will be structured based on the Fear and Belief Avoidance Questionnaire (Table 1) which will serve as a guide for the sessions through a Powerpoint presentation. In addition, participants will be encouraged to stay active by walking for 20–30 min, 3–5 times a week and will be taught an exercise to improve the activation of the transverse abdominis (bracing or abdominal following). The PNE will be delivered by a physical therapist with four years of experience in this intervention. In addition, the same physical therapist will provide the therapy to both experimental groups to maintain the same patient-physical therapist relationship and not to influence the results due to this contextual aspect, so no adaptations were made for each group either.

**Table 1 table-1:** Summary content of pain neuroscience education.

**Dimension**	**Content**
Dimension 1: Approach	Introduction to the program.
	The objective of today’s session will be to contrast what we know about pain, with the scientific advances in rehabilitation through a conversation.
	Your opinion regarding each of the points that we will discuss is very important for your rehabilitation.
Dimension 2: Pain as protector (the big picture)	Pain as a multidimensional experience
	- Neurophysiology of pain: pain pathways, neuronal synapses, action potentials and pain perception. Gate of entry of pain.
	- Modulation of pain: explain the processes of facilitation and inhibition. The theory of gate control will be emphasized.
	- Acute pain and chronic pain: explain the differences between acute pain and chronic pain

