#### Treatment expectation

The treatment expectation questionnaire (TEX-Q) will be used. This is a generic multidimensional measure that allows evaluating the patient’s expectations in both medical and psychological treatments and allows comparing the impact of multidimensional expectations in different conditions. Its psychometric properties have yet to be determined, but it was developed through a rigorous procedure that incorporated complex and diverse literature and expectation evidence as well as peer review (Alberts et al., 2020).

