#### Data collection and management

Outcome measures will be collected at one-week before intervention, one-week post-intervention and four-weeks post-intervention (Fig. 2).

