### Data analysis

#### Statistical approach

The analysis of the data will be blinded, as each subject and condition will be coded by a consultant who will not be involved in the investigation. SPSS software version 25.0 will be used for all analyzes (SPSS Inc. Armonk, NY, USA). Data will be reported as mean with SD or median with interquartile range. Statistical analyzes were performed on an intention-to-treat basis, with imputation of missing data using the average of the remaining participants.

Normality tests will be performed using the Shapiro–Wilk test given the number of subjects needed for each group. In addition, the homogeneity of variance and the sphericity of the data will be determined. In the case of not assuming any of these assumptions, the Green-Hausser correction will be used for the interpretation of subsequent analyzes. A three-way repeated measures ANOVA will be conducted to analyze both primary and secondary outcomes. The factors considered in this analysis will include time and intervention. Additionally, the third factor will encompass variables such as employment status, education level, or income. In case of significant interaction, a two-way repeated measures ANOVA (time (pre-post) × intervention (in-group PNE, individually PNE, no intervention)) will be performed for each employment status (employed or unemployed). Furthermore, a two-way repeated measures ANOVA (time (pre-post) × intervention (in-group PNE, individually PNE, no intervention)) will be performed for each educational level (high or low). Lastly, a two-way repeated measures ANOVA (time (pre-post) × intervention (in-group PNE, individually PNE, no intervention)) will be performed for income (≤USD 545, or >USD 545). If interactions are detected in any of the 2-way ANOVAs, a *post-hoc* analysis will be conducted using multiple pairwise comparisons employing a *t*-test corrected by Bonferroni. The significance level will be set at 5%.

A stepwise multiple linear regression will be performed to estimate the influence of changes in primary and secondary outcomes. In each model, adjustments will be made for employment status, educational level, and income. In this analysis, the aforementioned variables will be sequentially incorporated into each model.

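### The protocol names treatment expectation as a possible influence on the results and collects a pre-intervention TEX-Q score, but no stated analysis uses that score as a covariate

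*Protocol article*

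**What the plan says.** **Role of expectation.** The abstract counts it among the outcomes: "The outcome measures will be fear avoidance and beliefs, pressure pain threshold, pain self-efficacy, catastrophizing, pain intensity, and treatment expectation". Under Secondary outcomes the protocol states "The treatment expectation questionnaire (TEX-Q) will be used" and describes a generic instrument that "allows evaluating the patient’s expectations in both medical and psychological treatments". That section adds that its psychometric properties are still to be established.

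**Timing.** Data collection and management says "Outcome measures will be collected at one-week before intervention, one-week post-intervention and four-weeks post-intervention", with no exception for TEX-Q. The abstract gives a different first follow-up (immediately after the intervention) but the same baseline visit, so a pre-intervention score is planned on either reading.

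**Analysis.** Statistical approach: "A three-way repeated measures ANOVA will be conducted to analyze both primary and secondary outcomes". Beyond time and intervention, "the third factor will encompass variables such as employment status, education level, or income". The stepwise regression adjusts for the same three social variables.

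**Acknowledged influence.** Limitations, giving as its reason that PNE is little known to the public, says "the expectation of the effectiveness of the therapy can significantly influence the results".

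**Context for the outcome role.** On the face-to-face part, Intervention says "This will be delivered in a single face-to-face session of approximately 60–80 min". Participants are also advised to walk and taught an exercise. They receive a brochure and five 15-minute videos, keep a calendar, and hand in a written task at the second assessment. Table 1 makes recovery expectations one of the five taught dimensions. The control arm is usual care in the abstract and no intervention in the Statistical approach. Randomization and blinding says participants are told they will receive education, without excepting controls.

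**The concern.** The protocol identifies a patient characteristic that it believes can move the results, schedules its measurement before treatment, and then leaves it out of every stated factor and adjustment set. The limitation is disclosed, but the data that could partly address it are not put to that use.

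At stake is the efficiency of the arm comparison in a small trial. With a few dozen people per arm, the arms can differ appreciably in baseline expectation by chance. If expectation does predict the response, an unadjusted comparison carries that difference as noise. A covariate fixed in advance removes part of it. One added after the data are seen invites doubt about why it was chosen.

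**Working it through.** **1. What treatment remains after the session.** The protocol gives a total intervention time of 135–155 min. The session is 60–80 min and the videos are 5 × 15 = 75 min, so 60 + 75 = 135 and 80 + 75 = 155. The stated total is reproduced exactly, which shows that the protocol counts the home videos as intervention.

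**2. Whether baseline TEX-Q is used anywhere.**
- ANOVA factors: time, intervention, and one of employment, education or income. Expectation is not named.
- Regression adjustments: employment, education, income. Expectation is not named.
- Regression subject: changes in primary and secondary outcomes, in a role that is not clearly stated. Change in TEX-Q might enter here, but that is not the baseline score.

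**3. Inputs for the size.** The documents give no correlation between baseline TEX-Q and any outcome. I assume r = 0.2 to 0.4, meaning the correlation with the outcome contrast (for example, change in FABQ) after the terms already in the model. For arm size I use 20 (Sample size) to 33 (abstract) per arm; the article is not consistent on this, which is a separate matter.

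**4. Precision.** Residual variance is multiplied by 1 − r², and the standard error by √(1 − r²).
- r = 0.2: 1 − 0.04 = 0.96, a 4% fall; √0.96 = 0.980, about 2% off the standard error.
- r = 0.4: 1 − 0.16 = 0.84, a 16% fall; √0.84 = 0.917, about 8% off the standard error.

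**5. Chance imbalance.** The standard error of a difference in mean baseline TEX-Q between two arms, in SD units, is √(2/n).
- n = 20: √0.100 = 0.32 SD; n = 33: √0.0606 = 0.25 SD.
- An imbalance of one standard error moves the unadjusted contrast by r × √(2/n): from 0.2 × 0.246 = 0.05 SD to 0.4 × 0.316 = 0.13 SD.

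This movement is random in direction and already included in the unadjusted standard error. It is not bias.

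**6. Cost.** Estimating one slope inflates the variance by an expected factor of about 1 + 1/(N − k − 2), with k = 3 arms.
- N = 60: 1 + 1/55 = 1.018; N = 99: 1 + 1/94 = 1.011.
- Net at N = 60: r = 0.2 gives 0.96 × 1.018 = 0.977, standard error down about 1%; r = 0.4 gives 0.84 × 1.018 = 0.855, down about 7.5%.
- If r were zero, the standard error would rise by about 0.9% (√1.018 = 1.009).

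**The case against.** **Covariate choice is often left to an analysis plan, and disclosing a limitation does not oblige adjustment.** Both are true. But the article does not leave the adjustment set open: it lists three variables and omits the one it singles out as influential. That makes this an improvement to a stated choice, not a complaint about missing detail.

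**Randomisation already protects the comparison.** This stands. A reader might infer that leaving out baseline expectation biases the FABQ result. It does not: chance imbalance is covered by the standard error and the type I error rate.

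**TEX-Q is unproven and the gain rests on an assumed correlation.** This also stands in part. The protocol says only that expectation can influence results and concedes that the instrument's properties are not yet known. The gain may be near zero, but the downside is then about 1% on the standard error.

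**A reader might go further and infer that TEX-Q should not be an outcome at all, because no treatment remains to be expected after one session and controls receive none.** The documents do not support that. Walking, the exercise, the brochure and the videos continue after the session, and the videos are counted in the intervention time. Recovery expectations are a taught dimension, so change in expectation is a coherent target. The two PNE arms receive identical content, so their comparison is meaningful. The abstract gives controls usual care, which a generic instrument can rate. What remains is that the article does not make clear what controls are rating at follow-up.

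**Conclusion.** The point holds as a modest, nearly free improvement. The protocol treats expectation as influential, collects it before the intervention, and does not use it in comparing the arms. Under an assumed r of 0.2 to 0.4, adjustment would reduce residual variance by 4 to 16% and the standard error by about 2 to 8%, slightly less once the estimated slope is paid for. The benefit is precision and correction of chance imbalance, not removal of systematic bias. No stated sample size or planned conclusion depends on it.

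The statement that the plan never accounts for expectation in any form would be too firm, because the role of changes in secondary outcomes in the regression is unclear. If change in TEX-Q does enter there, it would not serve the same purpose: scores after the session can be affected by allocation, and conditioning on them could remove part of the effect under study.

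TEX-Q may stay a secondary outcome. Its follow-up contrast with the control arm should be read with caution until the control arm is described consistently.

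**What to change.** In the Statistical approach, prespecify the pre-intervention TEX-Q score as a covariate in the between-arm models for FABQ and every other outcome except TEX-Q itself. In the repeated measures models, let its effect differ by time: a covariate with the same effect at every visit cancels out of within-person change and so leaves the time × intervention test unadjusted. State that the score is taken before allocation is disclosed, and that post-session TEX-Q will not be used for adjustment.

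Keep TEX-Q as a secondary outcome, and add a sentence that its contrast with the control arm will be interpreted cautiously. Reconcile the abstract (usual care), the Statistical approach (no intervention) and Randomization and blinding (what participants are told), so that it is clear what controls are rating.

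The cost is a few sentences of wording and about one degree of freedom per model (one per time contrast in a repeated measures model). No extra data or visits are needed. A participant without a baseline TEX-Q score would need the missing-data rule to cover the covariate.

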## Supplemental Information

10.7717/peerj.17507/supp-1Supplemental Information 1CONSORT checklist

10.7717/peerj.17507/supp-2Supplemental Information 2Trial protocol
